### Run-in

To ensure that they were fully committed to the trial before randomisation and had no reaction to the excipients in the trial medication, participants were asked to complete a run-in period of approximately twelve weeks. At the entry to run-in visit the nurse recorded symptoms, blood pressure, weight, urinary protein, glucose and blood and checked that the woman remained eligible for the trial (see Additional file 1). The GP conducted a general medical examination and made the decision on eligibility. The nurse ensured that the procedures for the trial and possible risks and benefits were understood by the women and that all questions had been answered.

Those willing to enter the trial gave written informed consent and were issued with tablets for the run-in phase. All women took medication during the run-in: women who were eligible for the placebo controlled randomisation (strata 1 and 3) took placebo; those who were not (stratum 3) took estrogen only HRT.

Participation in the National Breast Screening Programmes was encouraged but was not mandatory; advice and information on breast awareness was given. Women with a uterus were given diaries to record any vaginal bleeding, concurrent medication and illnesses. All patients received a card stating that they were in the trial with contact details for the practice, the co-ordinating centre and, for use by medical staff, the telephone number for the 24 hour emergency code break.

There were two visits to the surgery during the run-in period, at approximately three and eight weeks after entry, mainly to check on tablet compliance and ensure that the woman remained eligible (Table 1). At the second run-in visit, those reaching 80% compliance were invited to enter the randomised phase of the trial. If patients were willing to enter but had not reached 80% compliance one further run-in was permitted.

In the UK these women were asked to give a blood sample to assess the last criterion for eligibility, a fasting triglyceride level < 5.5 mmol/l, and to provide samples for future analyses. A 25 ml non-fasting blood sample was taken initially: 5 ml for immediate estimation of triglyceride and cholesterol levels and 20 ml to store as serum, red blood cells, buffy coat and plasma for future analyses. Samples were prepared at the practices and posted to arrive within 24 hours at the trial co-ordinating centre for analysis. Patients with a non-fasting triglyceride level > 5.5 mmol/l were recalled for a second triglyceride measurement following an overnight fast. Patients with fasting triglyceride levels ≥ 5.5 mmol/l were excluded from the trial and advised to consult their GP. In Australia and New Zealand, this criterion for eligibility was waived. Women who were unwilling to give a blood sample in the UK could enter the trial without a blood sample if their GP had agreed eligibility.

### Randomisation

After the second run-in visit women who were eligible and willing to participate were randomised centrally and appropriate medication dispatched to the practice in time for the baseline randomisation visit. Participants were assigned to treatment in accordance with the schema at Figure 3 using a computer based, stratified block randomisation program to ensure that within each stratum the treatment groups were of virtually equal size. The stratification was based on hysterectomy status and HRT use at the time of randomisation. In stratum one, women with a uterus were randomised to combined HRT therapy using a block size of 16. In stratum two, hysterectomised women who were only prepared to take active treatment were randomised to estrogen only HRT or combined HRT using a block size of 16. In stratum three, hysterectomised women were randomised to estrogen only HRT, combined HRT or placebo using a block size of 24.

The baseline questionnaire at the randomisation visit (see Additional file 1) covered risk factors, possible adverse events, all outcomes, quality of life and other medical history to check that they remained eligible. Use of health services and details of the severity of certain conditions eg, systemic lupus erythematosus were obtained from the patients' notes. The nurse measured height, weight, and waist and hip circumference using standard operating procedures and the GP then made a final decision on eligibility. A patient was recorded as entering randomised treatment if she left the surgery with her first pack of randomised treatment tablets.

### Blinding and protection from bias

As far as possible, the trial was conducted in a double-blind manner. The treatment assignment was directly accessible only to the computer officer responsible for the randomisation, the trial statisticians and the staff supplying a 24 hour code break service. Computer generated lists were sent to the drug dispensing manager along with patient labels. Active and placebo medications were matched for size, colour and taste. Within each stratum labelling and packaging was identical and randomly generated tablet identification codes were used so that the participant, the nurse and the GP were blinded to the treatment allocation. No-one involved with assessment of outcomes was aware of treatment assignment. During the trial it was not possible to maintain full blindness as reports of vaginal bleeding or spotting triggered a code break and an investigation to ensure that any abnormal bleeding was not overlooked.

### Interventions

Estrogen-only HRT was conjugated equine estrogens (Premarin, Wyeth Ayerst), 0.625 mg orally daily. Combined progestogen and estrogen HRT was conjugated equine oestrogens as above plus medroxyprogesterone acetate (MPA) 2.5 mg orally daily (Prempro, Wyeth Ayerst US). Women with a uterus within three years of their last period, or aged 50–53 years, or aged 54 or over with unacceptable breakthrough bleeding took a higher dose of 5.0 mg MPA (Premique, Wyeth Ayerst). Women who experienced unacceptable intermittent spotting or bleeding with combined HRT containing 5.0 mg MPA were offered open label Premique cycle (Premarin 0.625 mg orally daily plus MPA 10 mg orally for the last 14 days of a 28 day cycle). Women could choose to remain on Premique cycle for the remainder of the trial or could return to their continuous combined treatment. Estrogen-only HRT, combined HRT and matched placebo containing the same excipients were prepared and supplied by Wyeth Ayerst US.

### Follow-up

It was planned to recruit women over a three year period and to end the trial nine years after the last participant was randomised giving a median of 10.5 years follow up, and a maximum of 12 years. Women were to be seen at their general practice at 4, 14, 27, 40 and 52 weeks and then 6 monthly. Nurses contacted participants between visits, by telephone, to provide advice and support as required. A final visit was to take place as soon as possible after the closure of the trial.

Because of the decision in October 2002 to close the trial early when the WHI results indicated that the likely balance of risks and benefits of HRTwas unfavourable the median follow up time for WISDOM was 11.9 months (IQR: 7.1 months to 19.6 months).

Patient compliance was assessed at each visit by tablet count. At the annual visit information was collected on risk factors, possible adverse events, all outcomes and on other medical history to check that patients remained eligible (see Additional file 1). At other visits information was collected on risk factors, possible adverse events, primary and secondary outcomes and on other medical history to check that patients remained eligible (see Additional file 1). There was provision for recording information received by the nurse or the GP from the patient, and with the patient's permission, from a friend or a relative between follow-up visits. A further check of general practice medical records was made annually.

Outcomes were assessed at face to face interviews between the patient and the nurse, using validated questionnaires wherever possible, and entering data directly onto laptop computers using a suite of software specially designed for the trial which included a real time patient management system in accordance with the protocol. Electronic data checking at the time of collection incorporated extensive checks for plausibility, consistency and completeness. Data were sent to the co-ordinating centre within one week of collection by modem link within the UK and via a standard File Transfer Program server site from Australia and New Zealand. A member of the study team, who was blinded to treatment allocation, obtained any data needed to confirm a clinical event from the GP, hospital or coroner.

It had been planned to ascertain fatal end-points and cancer registrations in the UK via the National Health Service Central Register, in Australia via the National Death Index database and in New Zealand via National Health Index number tracing, death registrations, hospital records and the New Zealand Cancer register but with the early closure this was not pursued.

To fully assess the long-term effects of HRT and to investigate changes following discontinuation of treatment, follow up by medical records in the general practice and national records had been planned for a further five years after treatment but following closure these plans were abandoned.

### Outcomes

The primary outcomes were:

• major cardiovascular disease, defined as the sum of one or more of fatal and non-fatal myocardial infarction, unstable, hospitalised angina and sudden coronary death;

• osteoporotic fractures (hip, wrist and all fractures other than skull, face, cervical spine, fingers and toes);

• incidence of breast cancer; and

• quality of life and psychological well-being;

Secondary outcomes were:

• breast cancer mortality;

• other cancers, incidence and mortality;

• venous thromboembolism (deep vein thrombosis, pulmonary embolism, retinal vein occlusion; and

• cerebro-vascular disease.

The following conditions were also investigated: depression; incontinence; symptomatic arthritis; tooth loss; periodontal disease; tinnitus; asthma; low back pain; age-related macular degeneration; cataract; and dry eye syndrome. Use of health services was recorded to allow an estimate of the health economic implications of HRT usage.

### Health economic analysis

It had been planned to evaluate the health economic implications of HRT by estimating, and modelling where necessary, costs of treatment, costs of conditions prevented or caused by HRT, costs of all use of health care and indirect costs such as time lost from work/usual activities and social security implications. Overall cost effectiveness was to be calculated as costs per Quality Adjusted Life Year (QALY) gained using the quality of life measured by the EuroQol. In the light of the early closure this analysis did not proceed.

### Dementia and cognitive decline sub-study

In an add-on study in sub-samples of WISDOM participants, the effects of HRT on the incidence and progression of dementia and on the onset and progression of cognitive decline were assessed. This work was led by [name] (Institute of Psychiatry, London), [name] (Psychiatry, Cambridge) and [name] (University College, London) and will be described in a separate publication.

### Confirmation of outcomes

Primary and secondary clinical outcomes were reviewed blind to treatment allocation. For cardiovascular disease, cerebrovascular disease, venous thromboembolism and cancers this was done by an independent assessor. For fractures the assessment was done by a member of the study team with a 10% sample reviewed by an independent assessor.

### Adverse events

An adverse event was defined as any untoward medical occurrence regardless of whether a causal relationship with trial treatment was suspected. The event was classified as serious if it was life-threatening, required inpatient hospitalisation or prolongation of existing hospitalisation, or caused significant or persistent disability or incapacity. An unexpected adverse event was an experience not previously reported (in nature, severity or incidence) in connection with the trial treatment. For confirmed serious adverse events which were trial exclusions, the protocol required either a permanent or a temporary interruption of trial treatment (see Additional file1). Where the protocol did not specify a course of action the nurse informed the GP and the trial clinician by memo and they liaised to decide what action to take. Whenever possible, the GP and clinician remained blind to treatment allocation. For minor adverse events, for example those recorded on the symptoms questionnaire, the nurse and, if necessary, the GP, advised palliative treatments, using guidelines, with the aim of keeping the patient in the trial on their randomised treatment. New onset migraine and current thrombophlebitis triggered a temporary interruption of treatment.

### Vaginal bleeding in women with a uterus

Intermittent vaginal bleeding was expected as a temporary side effect of continuous combined HRT in some women with a uterus randomised to PERT. Bleeding in women with a uterus was monitored by asking the women to complete a daily diary noting episodes of bleeding according to the following categories:

• spotting – spotting/streaking not requiring sanitary protection;

• light – small amount of bleeding requiring some protection;

• moderate – less than a normal period;

• severe – normal period or heavier;

and recording any concurrent medical conditions, medication and whether trial medication had been missed.

The diaries were monitored at scheduled visits and between scheduled visits women were asked to telephone the trial nurse to report bleeding. The trial nurse recorded occurrence of bleeding, severity, duration and whether bleeding was continuous or intermittent.

At the beginning of the trial, best practice advice suggested that to ensure that pathological bleeding was not overlooked, all reports of vaginal bleeding continuing for at least four weeks (continuous or intermittent) or bleeding over a shorter period which was considered to be severe, continuous or rapidly worsening, should trigger a request by the trial nurse for a break in the treatment code. Those taking placebo would then be referred to the GP, those taking combined HRT with 2.5 mg MPA offered 5.0 mg MPA, and those already taking 5.0 mg MPA asked to continue taking trial treatment for a further six weeks. Then, if bleeding continued, participants would be referred to the GP for investigation. If nothing abnormal were found, participants would be offered second line treatment with Premique Cycle. Women reporting only spotting would be monitored without a code break and the advice of the GP sought. This approach resulted in many women withdrawing themselves from randomised treatment as they were not prepared to wait for a protocol code break.

In January 2001, after consulting with the Steering and Data Monitoring Committees, procedures for the management of bleeding were revised to reduce withdrawals from the trial

To ensure that pathological bleeding was not overlooked, all reports of vaginal bleeding, including spotting, triggered an immediate break in treatment code. Patients were asked to continue on trial medication during an investigation of bleeding.

• Bleeding that started on placebo treatment

Women randomised to placebo were referred immediately to their GP for investigation in line with their usual clinical practice.

• Bleeding that started on active treatment

The management of women on active treatment depended on when bleeding occurred relative to treatment and previous amenorrhoea.

• Bleeding that started within 90 days on active treatment.

Vaginal bleeding is very common in the first few months on continuous combined hormone replacement therapy but usually resolves. Women with bleeding starting in the first 90 days of active treatment (excluding any treatment interruptions) were referred to their GP only if they or their nurse were concerned. Women taking 2.5 mg MPA were offered a dose increase to 5 mg as soon as bleeding was reported. Women already on 5 mg MPA had no change to their medication. Patients were monitored by the nurse for 90 days from the date bleeding started. Any woman who experienced vaginal bleeding after the 90-day monitoring period was referred to her GP.

It was recommended that women whose dose of MPA was increased to 5 mg because of bleeding in the first 90 days remained on the higher dose until 3 months amenorrhoea had been achieved. Thereafter the dose could be reduced to 2.5 mg, but should bleeding reoccur within 21 days of the dose reduction, it was recommended that the patient resume taking 5 mg MPA.

• Bleeding that started after 90 days amenorrhoea on active treatment.

Women with bleeding that started after 90 days of amenorrhoea on active treatment were referred immediately to their GP unless the bleeding occurred within 21 days of a treatment interruption, reduction in the dose of MPA from 5 mg to 2.5 mg or following diarrhoea, vomiting or a course of antibiotics. If one of these possible reasons applied, the patient was monitored by the nurse and referred to her GP if bleeding continued beyond 21 days.

• Persistent bleeding

Women with persistent bleeding for which no pathological cause was found were offered second-line treatment using Premique Cycle. Women with a uterus taking second-line treatment who reported bleeding which was heavier than their monthly menstrual bleed had been pre-menopause or of longer duration were referred to the GP for investigation.

### Vaginal bleeding in women with a hysterectomy

Women with a hysterectomy (sub-total or total) reporting vaginal bleeding were referred immediately to their GP for investigation.

### Discontinuation of trial treatment

Permanent discontinuation of trial treatment was required if any of the exclusion criteria for the trial were confirmed during follow up. If participants developed symptomatic or active gall bladder disease a temporary interruption of treatment was made and if the participant subsequently had a cholecystectomy they were invited to recommence trial treatment. A temporary interruption of treatment was required to investigate sudden loss of vision, onset of proptosis or diplopia.

When trial outcomes occurred that were not trial exclusions (myocardial infarction, unstable hospitalised angina pectoris, cerebrovascular accident, subarachnoid haemorrhage, TIA, osteoporotic fractures) participants were able to remain on their allocated treatment to contribute to other outcomes. However, a temporary interruption of treatment could be initiated at the discretion of the GP or other clinician or by the participant. To reduce the risk of venous thromboembolism, a temporary interruption could be made during hospitalisation and following accidents resulting in immobilisation. Trial treatment could also be discontinued at the discretion of the GP for symptoms possibly associated with trial treatment, other medical or non-medical reasons. Participants were free to initiate withdrawal from the trial or temporary interruption of treatment without giving a reason.

GPs and participants were encouraged to try a temporary interruption of treatment first and were requested to discontinue treatment permanently only after consultation with the trial clinician and after all efforts had been made to keep the patient on randomised treatment.

### Minimising loss to follow up

All patients who discontinued trial treatment were followed up and every effort was made to contact patients after non-attendance at follow up appointments to minimise losses to follow up. Where participants did not attend for visits, but had given permission for their medical records to be accessed, annual and final searches were undertaken.

### Sample size and comparisons

The original minimum sample size for WISDOM, set at the time of the grant application, was 18000, to detect, with 80% power at the 5% level of significance, a 25% decrease in ischaemic heart disease (excluding unstable angina) and stroke over ten years comparing, in women aged 50–64 years at randomisation, those randomised to HRT (combined HRT plus estrogen only HRT) with those randomised to placebo. It was agreed that an actual recruitment target of 23000, to include recruitment from countries other than the UK, was feasible.

The primary outcome was subsequently changed to exclude stroke and include unstable angina and the age range was extended up to 69 years. Other assumptions were modified reflecting falling coronary event rates in the general population, new information from the Women's Health Initiative (personal communication to MRC WISDOM Steering Group) on likely times to treatment effects and fall off in treatment effects after discontinuation of treatment, and revised estimates for withdrawal from randomised treatment. Sample size calculations were revised to calculate what might be detected with a sample of 23000. Comparing combined HRT with placebo it was estimated that WISDOM would have 80% power at the 5% level of significance to detect at ten years:

• for cardiovascular disease (including unstable angina), a 29% reduction from a placebo event rate of 39/1000;

• for all osteoporotic fractures, a 20% reduction from a placebo event rate of 95/1000; and

• for breast cancer, a 40% increase from a placebo event rate of 36/1000.

For cardiovascular disease calculation of event rates in the trial population not receiving active treatment incorporated the following.

• Over the period 1997 to 2010 an assumed reduction in mortality from IHD of 40% and drop in incidence rate of 20%.

• Withdrawal from randomised treatment by 10% of participants in the first year of treatment, 7% in year 2, 4% in year 3, 3% in year 4 and 2% in years 5 – 10, giving a total withdrawal at some stage of 36%. An approximation to the change in the event rate observed can be made assuming 70% of HRT group have been on treatment for full 10 years and 30% have no treatment.

• For IHD 2.5 non-fatal events occurring for each fatal event as suggested by the MONICA study, total numbers (i.e. fatal plus non-fatal) then being derived from ONS age-specific mortality rates in 1997.

• In the absence of reliable estimates of the incidence of unstable angina for women in the relevant age group, the best estimate was a rate of about 1 per 1000 women per year. Over the ten years of the trial this rate would generate 9.7 unstable angina events per 1000 women entered. However, it was estimated that 50% of these would lead to myocardial infarction, giving an incidence of independent unstable angina events of 4.8 per 1000 women.

• A healthy volunteer effect leading to event rates only 67% of those based on the sum of fatal and non-fatal episodes in the general population.

• Based on feasibility studies and current use of and interest in HRT 20% of the trial population being in the age range 65–69 years and 80% being distributed equally across the three five year age bands, 50–54, 55–59, 60–64 years.

• A 3 year recruitment, which would give 33% of women in study for 11 years, 33% in study for 10 years and 33% of women in study for 9 years.

Using these assumptions the average probability of a major cardiovascular event within ten years in women in the age group 50–69 was estimated to be 0.039.

For the main comparison of HRT versus no HRT, only women who could be randomised to receive placebo could contribute (strata 1 and 3, Figure 3). Based on feasibility studies the proportions expected in the different strata were: stratum 1, 58% equally divided between combined HRT and placebo; stratum 2, 22% equally divided between combined HRT and estrogen-only HRT; stratum 3, 20% equally divided between combined HRT, estrogen-only HRT and placebo. The majority of women on HRT (~84%) would be on combined HRT. Of the total sample size, 78% would be used to compare HRT with placebo (the remaining 22% contributing to the ERT v PERT comparison). The sample sizes have been calculated to achieve significance in a combined HRT versus no HRT comparison, with equal numbers of women randomised to combined HRT and placebo. The target sample size of 22300 gives statistical power of 80% (at 5% level of significance) to detect a reduction of 29% in the cardiovascular end-point. Power for an HRT (combined HRT plus estrogen only HRT) versus no HRT comparison would be slightly increased by the inclusion of hysterectomised patients (within stratum 3) randomised to estrogen-only HRT.

A 29% reduction in risk in those taking HRT would reduce the average probability of a cardiovascular event to 0.028, an absolute reduction of 0.011. If this was achieved then treating 89 women for ten years with HRT would prevent one cardiovascular event. Allowing for withdrawals as described above the average probability of an event would be 0.031 and an intention to treat 125 women for ten years with HRT would prevent one cardiovascular event.

For a direct comparison of estrogen only HRT with combined HRT, approximately 8,000 women could contribute: those in stratum 2 together with those in stratum 3 randomised to HRT. With equal numbers being randomised to estrogen only HRT and combined HRT a 45% difference in cardiovascular events between the groups could be detected with statistical power of 80% (at 5% level of significance).

For the osteoporotic fracture and cancer outcomes it was assumed that the final assessment would be made five years after the end of treatment. No assumptions were made about HRT use following the end of the trial.

In estimating the trial event rate for fractures it was assumed there would be no change in the current fracture rate until 2010. Incidence rates for hip fracture were estimated using figures from the European Report on Osteoporosis, 1998. No trend figures were available and no trend was assumed. Rates were reduced by 20% for a healthy volunteer effect. At the end of the 5 year post treatment follow-up period, 27 hip fractures per 1000 women recruited would be expected. Based on published data the risk ratio was estimated as 0.7 in the first year on treatment, 0.6 for second year, 0.5 for years 3 – 10, gradually increasing back to 1 after treatment ends. This would give an expected reduction in events of 26% from 27 per 1000, to 20 per 1000 women recruited. The sample size of 23000 would be able to detect only a larger reduction in hip fractures of 36% with 80% power at the 5% level of significance. We therefore looked at all osteoporotic fractures. As there were no UK incidence rates available for all osteoporotic fractures we assumed the same ratio between hip and all osteoporotic fractures as in US. Rates were reduced by 20% for a healthy volunteer effect. At the end of 5 year post treatment follow-up period, 95 fractures per 1000 women recruited would be expected. Assuming the risk ratio for all fractures was similar to that for hip fractures a 28% decrease in event rate at 5 year follow-up would be expected. A sample size of 23000 could detect a smaller reduction of 20% for all osteoporotic fractures.

The incidence rate for breast cancer rose by about 50% in those aged 50 -69 years over the period 1982–1992. In estimating the trial event rate for breast cancer it was assumed that no further increase would occur. Incidence rates were adjusted down by 10% to allow for the fact that those with near relatives having had breast cancer were unlikely to enter the trial. No other healthy volunteer effect was allowed for. With these assumptions, the expected trial event rate for breast cancer at the end of the 5 year post treatment follow-up period was 36 per 1000 women entered. With a sample size of 23000 it would be possible to detect a 40% increase from a placebo event rate of 36/1000 women-years. This was much higher than the expected increased risk; observational studies suggested that the risk ratio increased by 2.3% for each year on treatment and reduced by the same amount after treatment ends. This would give an expected 11% increase in event rate at 5 years follow-up, an increase from 36 per 1000 women to 40 per 1000 women recruited. It was thus anticipated that WISDOM data would be most appropriately used to contribute to a meta-analysis of the effect of HRT on breast cancer.

The incidence rates for colorectal, ovarian, cervical and endometrial cancers are low and WISDOM would be able to detect only very large increases/decreases associated with HRT use. Estimated event rates for other cancers at 5 year post treatment follow-up were: colorectal 19 per 1000 women recruited; ovarian 8 per 1000 women recruited; cervical 3 per 1000 women recruited; and endometrial 6 per 1000 women recruited.

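### At 22,300 women the stated strata give combined HRT versus placebo about 76–78% power, not the stated 80%; pooled HRT versus placebo reaches about 80%, and 23,000 is quoted for the same effect

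*Protocol article*

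**What the plan says.** All of the following is in the protocol article, Sample size and comparisons.

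- **The sized comparison.** "The sample sizes have been calculated to achieve significance in a combined HRT versus no HRT comparison, with equal numbers of women randomised". The two groups meant are placebo and combined HRT.
- **The claim.** "The target sample size of 22300 gives statistical power of 80% (at 5% level of significance) to detect a reduction of 29" per cent in the cardiovascular end-point.
- **The share.** "Of the total sample size, 78% would be used to compare HRT with placebo".
- **The expected strata.** Stratum 1 is 58% of women, split equally between combined HRT and placebo. Stratum 2 is 22% and has no placebo arm. Stratum 3 is 20%, split equally between combined HRT, estrogen alone and placebo.
- **The sentence after the claim.** It describes the stratum 3 women on estrogen alone as an addition that slightly raises power for the pooled HRT comparison.
- **The second total.** Earlier in the section: "Sample size calculations were revised to calculate what might be detected with a sample of 23000". Power is then stated in these terms: "Comparing combined HRT with placebo it was estimated that WISDOM would have 80% power at the 5% level of significance to detect at ten years". The first effect listed under that sentence is this one: "for cardiovascular disease (including unstable angina), a 29% reduction from a placebo event rate of 39/1000".

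The Abstract and Results give 22,300 as the target. The fracture and breast cancer calculations use 23,000.

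**The concern.** In the text, the women on estrogen alone are outside the sized comparison and would add power only to the pooled one. In the arithmetic, 22,300 comes out almost exactly when they are counted as if they were on combined HRT or placebo, that is, when the whole 78% is split in two. If so, the figure printed for combined HRT versus placebo is in effect that of the pooled comparison.

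The Statistical methods section keeps the two comparisons apart, so a reader needs to know which of them the 80% belongs to. The same effect, event rate, power and comparison are also attached to two different totals, and the reader cannot tell which one the design rests on.

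**Working it through.** **Inputs from the article**
- Placebo probability: "the average probability of a major cardiovascular event within ten years in women in the age group 50–69 was estimated to be 0.039".
- Dilution: 70% of the HRT group treated throughout and 30% untreated, so p2 = 0.039 × (1 − 0.29 × 0.70) = 0.03108. The article prints 0.031 after withdrawals.
- 5% significance, 80% power. Two-sided testing is my assumption, as the article does not state sidedness; one-sided testing does not reproduce 22,300 at either share.

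Without dilution (p2 = 0.0277) the total would be only about 10,100 to 11,600, so the dilution was evidently applied.

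**Step 1: shares**
- Each of combined HRT and placebo: 29% + 20%/3 = 35.67%. Together 71.33%. At 22,300: 0.3567 × 22,300 ≈ 7,954 per arm.
- Strata 1 and 3 entire: 58% + 20% = 78%. Split in two: 0.39 × 22,300 = 8,697 per arm.
- Check: 35.67/(35.67 + 6.67) = 84%, the proportion that the article gives for women on HRT who take the combined form. The 78% therefore includes the 6.67% on estrogen alone.

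**Step 2: reproducing the plan's figure**

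Per arm, with d = p1 − p2 and p̄ the mean of p1 and p2:

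n = [1.960·√(2p̄(1−p̄)) + 0.842·√(p1(1−p1) + p2(1−p2))]² / d²

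With d = 0.00792 and p̄ = 0.03504, n = (0.5097 + 0.2188)² / 0.00792² ≈ 8,467. With continuity correction, n/4 × [1 + √(1 + 4/(nd))]² ≈ 8,718.

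| p2 | Correction | n per arm | Total at 78% | Total at 71.33% |
|---|---|---|---|---|
| 0.03108 | no | 8,467 | 21,711 | 23,740 |
| 0.03108 | yes | 8,718 | **22,354** | 24,443 |
| 0.031 | no | 8,283 | 21,239 | 23,224 |
| 0.031 | yes | 8,531 | 21,875 | 23,919 |

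The corrected calculation at 78% gives 22,354, within 0.3% of 22,300. At 71.33%, every entry is about 920 to 2,140 women above 22,300.

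**Step 3: power at the stated totals**

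Power = Φ{[d − 1.960·√(2p̄(1−p̄)/n)] / √[(p1(1−p1) + p2(1−p2))/n]}; the continuity correction subtracts 1/n from d.

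For n = 7,954 and p2 = 0.03108: Φ[(0.00792 − 0.00572)/0.00292] ≈ 77.5%; corrected, 76.2%.

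In the table, the first figure in each cell is uncorrected and the second corrected.

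| Comparison | p2 = 0.03108 | p2 = 0.031 |
|---|---|---|
| Combined vs placebo, 22,300 (7,954 per arm) | 77.5% / 76.2% | 78.4% / 77.1% |
| Whole 78% split 1:1, 22,300 (8,697 per arm) | 81.0% / 79.9% | 81.9% / 80.8% |
| Pooled HRT (9,440) vs placebo (7,954), 22,300 | 80.9% / 79.8% | 81.7% / 80.6% |
| Combined vs placebo, 23,000 (8,203 per arm) | 78.7% / 77.5% | 79.6% / 78.4% |

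The pooled row applies the same effect to the women on estrogen alone.

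**Step 4: detectable effect**

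With 7,954 per arm, 80% power corresponds to an intention-to-treat reduction of 20.9%, or 20.9/0.70 = 29.9% on treatment. With continuity correction the figures are 21.2% and 30.3%.

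**The case against.** Four points can be made on the other side.

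1. **The dilution is approximate.** The article itself calls 70/30 an approximation. Its withdrawal schedule (10, 7, 4, 3, then 2% a year) leaves 90, 83, 79, 76, 74, 72, 70, 68, 66 and 64% on treatment, an average of about 74%. Weighting towards the later, higher-risk years would lower this, but only 72% is needed: p2 is then 0.0309, which still rounds to the printed 0.031, and 7,954 per arm gives 79.9% uncorrected. This stands. A reader might infer that 80% can be reached only by using the 78% share, but the article does not support that. The pooled comparison with its real unequal split also gives about 80%.

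2. **The gap is small beside the inputs.** The 0.039 rests on rough assumptions about unstable angina, the healthy volunteer effect and trends. A shift from 29% to about 30% is modest. This stands as to size. It does not make the printed figure follow from the printed inputs.

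3. **The main question is not underpowered.** A reader might infer that it is. The article defines the main comparison as HRT, mainly combined, against placebo, and that reaches about 80%. This stands. The error is in which comparison the figure is attached to.

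4. **Little now depends on it.** The two totals differ by about 3%, and the trial closed with 5,694 women randomised. That limits the consequence, but the published design statement still contradicts itself.

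**Conclusion.** The point holds in a limited form. The article assigns 80% power at 22,300 to combined HRT versus placebo, while its own strata and its own dilution give about 76–78%. That is a shortfall of about 2 to 4 percentage points, or a detectable reduction of about 30% instead of 29%. About 80% belongs to pooled HRT versus placebo.

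The most likely explanation is that the 78% share was divided in two, because that reproduces 22,300 to within 0.3%. It remains an inference, since slightly higher adherence would give nearly the same power at the correct share.

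The unexplained second total is a separate, smaller inconsistency. The 23,000 figure is close to adequate for the comparison named (about 77–80%), so having two totals does not show that either one is a wrong target.

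The result assumes two-sided testing at 5%, the stated strata proportions, and 70/30 dilution applied to a 29% on-treatment reduction.

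**What to change.** - State both results at 22,300: combined HRT versus placebo (about 7,954 per arm) has about 76–78% power for a 29% on-treatment reduction, roughly 20% by intention to treat; pooled HRT versus placebo has about 80%.
- Give the share of women and the adherence factor used. If a factor other than 70% lies behind the 80%, print it.
- Use one total throughout Sample size and comparisons, and quote the cardiovascular, fracture and breast cancer detectable effects at that total. Moving from 23,000 to 22,300 multiplies detectable effects by about √(23,000/22,300) = 1.016, so 20% becomes about 20.3% and 40% about 40.6%.

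The cost is a slightly less favourable stated power and some recalculation. Neither recruitment nor the analyses change.
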